### Process evaluation

A detailed process evaluation plan will be developed to evaluate the holistic screening for all complications of diabetes, including the teleophthalmology. For each quantitative outcome measure, we will systematically embed qualitative measures in each RE-AIM (reach, efficacy, adoption, implementation and maintenance) dimension to evaluate the implementation strategy of community screening with minimally invasive tests.^32 33^

### Outcomes

The primary outcome is the correlation of RBG levels and POC HbA1c levels. Secondary outcomes include the cut-off value of RBG to define prediabetes; diagnostic accuracy of risk stratification models for diabetes; prevalence and risk stratification for screening for DR; risk model for those at risk of complications of diabetes; identification of cost-effective diagnostic model for diabetes, prediabetes and complications of diabetes and process evaluation of minimally invasive community screening for diabetes and its complications.

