**Methods and analysis:**

This statistical and economic modelling study will be done on at least 48 000 prospectively recruited participants aged 40 years or above through community screening across 20 predefined regions in India. Each participant will be tested for capillary random blood glucose (RBG) and complete a detailed health-related questionnaire. People with known diabetes and all participants with predefined levels of RBG will undergo further tests, including point-of-care (POC) glycated haemoglobin (HbA1c), POC lipid profile and POC urine test for microalbuminuria, retinal photography using non-mydriatic hand-held retinal camera, visual acuity assessment in both eyes and complete quality of life questionnaires. The primary aim of the study is to develop a model and assess its diagnostic performance to predict HbA1c diagnosed diabetes from simple tests that can be applied in resource-limited settings; secondary outcomes include RBG cut-off for definition of prediabetes, diagnostic accuracy of cost-effective risk stratification models for diabetic retinopathy and models for identifying those at risk of complications of diabetes. Diagnostic accuracy inter-tests agreement, statistical and economic modelling will be performed, accounting for clustering effects.

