### Objectives

Our study has three important objectives. The first objective is to determine the ideal tests that could identify people at risk of diabetes and prediabetes in community screening that can be applied to LMIC. In order to accomplish this, we would evaluate the correlation of RBG levels with POC HbA1c levels and decide on a cut-off value for RBG from HbA1c to diagnose prediabetes. Second, we will evaluate whether initial triaging with NL diabetes risk score followed by either RBG or POC HbA1c only to the identified risk group is more effective than screening everyone for diabetes using either RBG or POC HbA1c. Third, we will develop affordable, easily deliverable and clinically effective model to accurately identify people at risk of complications of diabetes in community screening, especially DR.

Secondary objectives are aimed at guiding future policies on screening of diabetes and its complications. As the study involves a large sample and the setting up of a teleophthalmology model to screen for DR across 20 regions in India, we will be able to report the regional prevalence of DR and the associated risk factors, the inter-grader reliability and the accuracy of using artificial intelligence to grade DR. We will also conduct economic modelling and process evaluation of a holistic model for screening of all complications of diabetes. If sample size permits, we will be able to report on region-specific and diverse population-specific rates of diabetes and complications, visual impairment, quality of life and risk models specific to regions to inform local health authorities.

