### Study setting

This community screening will be conducted across 20 regions in India, each led by a local clinical centre with a trained ophthalmologist responsible for the study at that site (figure 1). Each region will have three clusters stratified into urban, rural and a predefined special category of population such as people with poor access to healthcare, or persons that are presumed to be at high risk or low risk of developing diabetes. The study will involve a door-to-door survey, with questionnaires and POC tests performed by fieldworkers. Each cluster will screen at least 800 consenting individuals aged 40 years or above for a cumulative sample size of a minimum of 48 000 participants. If any cluster or centre does not reach their target recruitment, it will be made up by another cluster or centre with the same stratified population.

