BP will be recorded in sitting position in the right arm to the nearest 1 mm Hg using the electronic OMRON machine (Omron Corporation, Kyoto, Japan). Participants with BP ≥140/90 mm Hg and not on antihypertensive drugs will be advised to contact a physician for further evaluation. A simple finger-prick test will be used to assess capillary RBG using a standard POC testing device (OneTouch Verio Glucometer, LifeScan Inc, USA). All participants with known diabetes or those with capillary RBG ≥160 mg/dL and 50 participants with RBG 110–159 mg/dL in each cluster will receive further tests. These include HbA1c estimation using a POC kit (A1c Now Plus, PTS Diagnostics, USA) and POC lipid estimation (Cardiochek PA analyser, PTS Diagnostics, USA). A POC urine sample (Chemstrip Micral dipstick, Roche Diagnostics, Mannheim) will be tested for the presence or absence of microalbuminuria.

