For the modelling framework, a marginal model with a logit link will be used, with retinal photograph determination of the reference outcome. Model-predicted probabilities will enable the area under the ROC curve to be estimated with 95% CI allowing for clustering, and accompanied by estimates of sensitivity, specificity, predictive values and likelihood ratios. Diabetes alone, and diabetes or prediabetes will be explored, as will already-identified and newly identified diabetes. For research questions on the diabetes diagnostic model, the denominator will principally be all those diagnosed with diabetes, whether already diagnosed or newly diagnosed. Interaction with this term (known vs newly diagnosed) will contribute to the analysis involving costs. Further modelling will explore use of the data from those that were found not to have diabetes or prediabetes.

Marginal logistic modelling will be used to identify the tests and questionnaire items which are most predictive, following a recommended approach.^28^ Continuous predictors will be handled using the fractional polynomial approach.^29^ In the sample size section, it can be seen that the dataset is large enough to allow models to assess up to 10 (reliably) and 20 (less reliably) dependent on intracluster correlation. Differences in area under the ROC curve and differences in specificity for given sensitivity will be estimated. The sample size is large enough to assess existing tests and to develop models. There may be limited scope to validate models. However, interim analysis will allow assumed rates and numbers to be assessed; the number of cases with STDR will be estimated more accurately, and this may enable more sophisticated forms of internal validation. Model validation would include calibration after model discrimination.^30^ Clustering within estimates of sensitivity, specificity and areas under the ROC curves will account for clustering, considering use of the non-parametric stratified bootstrap. A similar approach will be undertaken for the model to identify people at risk of complications of diabetes. Models for DR will also test the accuracy of artificial intelligence graded images compared with human graders.

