### Sample size calculation

The sample size is determined by considering the numbers of expected STDR, as this analysis will have the smallest number of cases with the outcome. With 20 regions, we expect 216 cases of STDR. From 48 000 people (2400 per centre) screened, of whom about 4800 are expected to be known diabetes and, we suspect, another 4800 will be newly detected diabetes. As 30% of the former group, and 15% of the latter group, are expected to have DR, we anticipated 2160 people to have DR, of whom 216 to have STDR.

Considering that some patients would come from the same family, and some from the same area, we assumed that outcomes at the area level would have an allowed intracentre correlation (ICC) coefficients of approximately up to 0.05 and to 0.10 for new and known diabetes, respectively. At the area level, with approximately 100 cases per region, and a working ICC of 0.075, we expect a design effect of 8.5. This calculation has been based on conservative allowances and approximations, which allow for deviations in the actual intracluster correlation coefficients from those anticipated, or for variation in the actual number of cases across centres. This means that the effective sample size (were the sample to be free from clustering) is 25 STDR cases for covariates, which are constant at the region level, or highly correlated among families within the same area. Using the rule of 10 people per covariate in order to plan the number of possible covariates, this implies that it will be possible to include 10–20 covariates (216/10) at the participant-level dependent on whether there is no, modest or moderately high ICC in the covariates, and 1–2 covariates (25/2) either at the area/family level for a stable diagnostic STDR model. All models will include observations at the participant level in order to accommodate participant-level covariates and will accommodate clustering further by including two area contrast terms; these reflect whether a participant lives in the strata of regions that are urban, rural or a special population. Models will be from the ‘marginal’ class so that correlation can be accommodated while importantly retaining a participant-specific interpretation of resulting estimates. The study will continue to recruit to enable process evaluation and other substudies to be incorporated.

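### People with known diabetes, tested for HbA1c at any RBG, are not kept out of the primary RBG–HbA1c correlation or the RBG cut-offs, and supply about 38% of the pairs

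*Protocol article*

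**What the plan says.** The protocol article's Outcomes section reads "The primary outcome is the correlation of RBG levels and POC HbA1c levels" and lists the RBG cut-off for prediabetes as a secondary outcome. The Objectives describe the same step: correlate RBG with POC HbA1c and "decide on a cut-off value for RBG from HbA1c to diagnose prediabetes". The Abstract puts the primary aim differently, as a model "to predict HbA1c diagnosed diabetes from simple tests that can be applied in resource-limited settings". None of these places restricts the analysis by prior diagnosis, and known diabetes is not an exclusion criterion.

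Study procedures decide who has an HbA1c value. The first group is "All participants with known diabetes or those with capillary RBG ≥160 mg/dL"; in addition, "50 participants with RBG 110–159 mg/dL in each cluster will receive further tests". On numbers, Study setting says "Each region will have three clusters stratified into urban, rural and a predefined special category of population" across 20 regions. The Sample size calculation takes 48 000 people screened, "of whom about 4800 are expected to be known diabetes", and a further 4800 newly detected.

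Statistical considerations mention known and new diabetes twice. They will be looked at separately on an exploratory basis, and for the diabetes diagnostic model "the denominator will principally be all those diagnosed with diabetes, whether already diagnosed or newly diagnosed".

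**The concern.** The tools are meant to find diabetes and prediabetes in people not yet diagnosed. The Introduction motivates them by the number of undiagnosed cases, and the Objectives place them in community screening. Someone already diagnosed is not a candidate for such a tool. The Introduction also describes HbA1c as an average of glycaemia over about three months. In a person with known diabetes that average reflects how well the condition is controlled, not whether it is present.

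Two consequences follow.

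- For the correlation, two differently selected groups are mixed: known cases taken at every RBG level, and people without known diabetes taken mainly because their RBG was high.
- For the cut-offs and accuracy estimates, a label based on HbA1c alone could place a known case with HbA1c below 6.5% in the prediabetes or normal group.

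Either way, the reported correlation or cut-off may not carry over to the people who would be screened.

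**Working it through.** **Step 1. The plan's own figures.** Screened: 20 regions × 3 clusters × 800 = 48 000, as stated. DR: 0.30 × 4800 + 0.15 × 4800 = 2160, as stated. STDR: 216, which is 216/2160 = 10% of DR. These figures are consistent. No sample size is given for the primary correlation, so there is no stated number of pairs to compare with.

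**Step 2. Who contributes a pair.** From Study procedures:

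| RBG (mg/dL) | Known diabetes | No known diabetes |
|---|---|---|
| below 110 | all | none |
| 110–159 | all | 50 per cluster |
| 160 or above | all | all |

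It follows, without any assumption about distributions, that every pair below 110 mg/dL comes from known diabetes. At 110–159 mg/dL, known cases enter in full while the others are capped.

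**Step 3. The share of pairs from known diabetes.** Inputs:

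- Known diabetes: K = 4800 (Sample size calculation).
- Sampled at 110–159 mg/dL: M = 20 × 3 × 50 = 3000, if every cluster fills its 50 with people without known diabetes.
- No known diabetes and RBG ≥160 mg/dL: H, which the document does not give. The base case sets H to the 4800 newly detected cases. The range 2000 to 9000 is an assumption.

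Share = K / (K + H + M); pairs left without known diabetes = H + M.

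| H | Total pairs | Share known | Pairs left |
|---|---|---|---|
| 2000 | 9800 | 4800/9800 = 49.0% | 5000 |
| 4800 | 12 600 | 4800/12 600 = 38.1% | 7800 |
| 9000 | 16 800 | 4800/16 800 = 28.6% | 12 000 |

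Among those screened, known diabetes is 4800/48 000 = 10%. It is therefore over-represented among the pairs by a factor of about 3 to 5 (28.6/10 to 49.0/10).

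**Step 4. How many known cases an HbA1c-only label could misplace.** The Introduction's bands are below 6.0% normal, 6.0–6.4% prediabetes and 6.5% or above diabetes. The document gives no control rate for known diabetes, so the fraction f with HbA1c below 6.5% is an assumption:

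- f = 10%: 0.10 × 4800 = 480, or 480/12 600 = 3.8% of pairs
- f = 30%: 0.30 × 4800 = 1440, or 11.4%
- f = 50%: 0.50 × 4800 = 2400, or 19.0%

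These are the people whose classification needs a stated rule. They are not a count of errors that the plan commits.

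**The case against.** The strongest reply is that the article leaves detail to a statistical analysis plan, due before database lock, and already intends to explore known and newly identified diabetes. Known status is recorded, so a restriction can still be applied. That is fair for analysis-set detail in general. But the article itself fixes the testing rule and an unrestricted primary outcome, and together these determine which pairs exist. The planned exploration sits in a logit framework with retinal photographs as the reference outcome, and the known-versus-new interaction is assigned to the cost analysis. Neither is tied to the correlation or the RBG cut-off.

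Three further points stand in full.

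- **Relabelling.** A reader might infer that controlled diabetes will be counted as prediabetes or normal. No sentence says so. The bands are background material, and where the article refers to known cases it treats them as having diabetes. What can be said is that nothing prevents such labelling. Table 1 makes POC HbA1c the reference for prediabetes, and the Abstract's target is diabetes as diagnosed by HbA1c.
- **The correlation has no categories.** Misclassification cannot affect it; only the mixing of differently selected groups can. Relabelling matters for the cut-offs and accuracy estimates.
- **The pooled denominator.** A reader might take "the denominator will principally be all those diagnosed with diabetes, whether already diagnosed or newly diagnosed" as proof that known cases are pooled into the diabetes cut-off. That does not follow. A model to diagnose diabetes cannot be fitted to people with diabetes alone, because it would have no non-cases. The paragraph opens with the retinal reference outcome, so the sentence plausibly belongs to the retinopathy model, where pooling is appropriate. The wording is loose and needs clarifying.

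**Conclusion.** The point holds in a limited form. As written, the primary correlation and the RBG cut-offs draw on a sample in which known diabetes supplies every pair below 110 mg/dL and about 38% of pairs overall. The first statement follows from the testing rule alone. The second rests on taking the newly detected cases as the RBG ≥160 mg/dL group and on full recruitment of the 50 per cluster.

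A reader might go further and infer that pooling must raise the correlation or move the cut-off by a known amount. The documents do not support that. They give no distribution of HbA1c or RBG, no treatment or control rate, and no RBG variability by diagnosis. The sign of the effect depends on such assumptions. The supportable conclusion is that the result would partly describe the wrong population, by an amount the documents do not determine.

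This should be settled in wording before database lock. No stated figure is wrong, and the STDR calculation does not depend on it.

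**What to change.** In Outcomes and Statistical considerations, or in the analysis plan with a cross-reference, state that:

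1. the primary RBG–HbA1c correlation, the RBG cut-offs and the evaluation of the diabetes risk score as a triage step use participants without known diabetes;
2. known diabetes is reported separately, as a description of glycaemic control;
3. known cases are always classified as diabetes in the analysis, whatever their HbA1c;
4. the denominator combining known and new diabetes applies to the retinopathy and complication models only.

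The cost is wording plus a smaller analysis set. The primary analysis loses about 4800 pairs and keeps about 7800 (5000 to 12 000 over the assumed range). No new data are needed, because known status already determines who is tested. The change does not remove the selection on RBG among people without known diabetes: they would still have no pairs below 110 mg/dL. That is a separate question.

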### Statistical considerations

The statistical methods will be developed fully within a statistical analysis plan, to be finalised before database lock. Diagnostic accuracy publications will follow recognised Standards for Reporting Diagnostic accuracy studies guidelines and the observational component will follow the Strengthening the Reporting of Observational Studies in Epidemiology guidelines. Table 1 shows the reference and index tests for diagnostic accuracy aspect of the study.

**Table 1 T1:** Reference and Index tests

Community screening for diabetes	
Reference standard	Index test
1. RBG	POC HbA1c Non-invasive diabetes risk scores
Community screening for prediabetes	
1. POC HbA1c	RBG Non-invasive diabetes risk scores
Community screening for complications of diabetes	
1. Serum lipid profile TC Non-HDL cholesterol LDL cholesterol HDL cholesterol TC:HDL ratio Triglyceride	Risk-based screening tool for complications of diabetes using minimally or non-invasive tests
2. HbA1c or RBG	
3. Microalbuminuria	
4. Retinal photography for retinopathy for all people with diabetes	

HbA1c, glycated haemoglobin; HDL, high density lipoprotein; LDL, low density lipoprotein; POC, point-of-care; RBG, random blood glucose; TC, total cholesterol.

Accuracy will be measured by sensitivity and specificity of tests to detect diabetes, prediabetes and people at risk of complications of diabetes. Clustering will be used to accommodate any over dispersion. Consistency of these statistics will be explored across centres and clusters (urban, rural and special population). Area under receiver operating characteristic (ROC) curve will be used to compare models representing the overall performance of tests under comparison. Refinement of test components (eg, combinations of tests or questionnaire items) will be developed, and internally validated where sufficient data are available. The number of false positives will be identified directly from the data. From the estimates of sensitivity and the specificity of diabetes risk score to detect prediabetic (or diabetic) and its estimated prevalence, it will be possible to estimate the false positive rate and the complement of the positive predictive value. All estimates will be accompanied by estimated 95% CIs, which account for both clustering and stratification.

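### The abstract and the Outcomes section name different primary endpoints, and the RBG–HbA1c correlation named in Outcomes neither answers the stated aim nor describes the screened population

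*Protocol article*

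**What the plan says.** Three parts of the protocol article bear on what is primary.

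- **Abstract, Methods and analysis:** "The primary aim of the study is to develop a model and assess its diagnostic performance to predict HbA1c diagnosed diabetes from simple tests". The RBG cut-off for prediabetes is listed as secondary.
- **Outcomes:** "The primary outcome is the correlation of RBG levels and POC HbA1c levels". The secondary outcomes include "diagnostic accuracy of risk stratification models for diabetes" and, again, the RBG cut-off for prediabetes.
- **Objectives:** the correlation is a step within the first objective: "we would evaluate the correlation of RBG levels with POC HbA1c levels and decide on a cut-off value for RBG from HbA1c", the cut-off being for prediabetes.

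Statistical considerations says how accuracy will be expressed: "Accuracy will be measured by sensitivity and specificity of tests to detect diabetes, prediabetes and people at risk of complications of diabetes", with the area under the ROC curve used to compare models. Table 1 in that section lists RBG as the reference standard for diabetes and POC HbA1c as an index test. For prediabetes it lists them the other way round.

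Study procedures says who receives POC HbA1c: "All participants with known diabetes or those with capillary RBG ≥160 mg/dL and 50 participants with RBG 110–159 mg/dL in each cluster". Participants without known diabetes and with RBG below 110 mg/dL are therefore not tested. Statistical considerations and Sample size calculation deal with clustering and stratification, but do not mention that HbA1c testing depends on RBG.

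**The concern.** The primary outcome should measure the primary aim. Here the aim is to classify people as having or not having HbA1c-defined diabetes, and the outcome is a correlation between two continuous measurements. The analysis that would answer the aim is demoted to secondary. The correlation is attached to the prediabetes cut-off, which the abstract and Outcomes both rank as secondary.

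The correlation also depends on the range of values sampled. Selecting people on RBG, one of the two variables correlated, changes it. Adding every person with known diabetes changes it again. The reported value would partly reflect the testing rule, and a reader would take it for a property of RBG in a screened community.

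**Working it through.** **1. The texts side by side.** Abstract: accuracy for HbA1c-diagnosed diabetes is primary. Outcomes: correlation is primary and diabetes accuracy secondary. Table 1: for diabetes, accuracy is judged against RBG. These cannot all hold.

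**2. Does a correlation determine accuracy?** Assume log-normal values in people without known diabetes: median RBG 112 mg/dL (log-SD 0.26), HbA1c log-SD 0.13, log-scale correlation 0.6 (0.59 on the raw scale). Only the median HbA1c is varied. The test is RBG ≥140 mg/dL against HbA1c ≥6.5%.

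| Median HbA1c | r | Sensitivity | Specificity |
|---|---|---|---|
| 5.3% | 0.59 | 0.66 | 0.833 |
| 5.6% | 0.59 | 0.56 | 0.857 |
| 5.9% | 0.59 | 0.47 | 0.885 |

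The same correlation is compatible with missing about a third or more than half of the cases.

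**3. Who is tested.** From the protocol: 20 regions × 3 clusters × 800 = 48 000. Known diabetes is 4800/48 000 = 10%, so 80 per cluster, leaving 720. At most 20 × 3 × 50 = 3000 people at 110–159 mg/dL are tested.

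**4. What the testing rule does to the correlation.** The protocol gives no RBG or HbA1c distribution, so these inputs are assumptions:

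- standardised bivariate normal values;
- 45/45/10% of people without known diabetes in the bands below 110, 110–159, and 160 or above;
- known diabetes shifted by 2 SD on both variables, with the same within-group correlation.

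Per cluster, 0.10 × 720 = 72 people are tested from the top band and 50 of 0.45 × 720 = 324 from the middle band, 122 in all.

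*Without known diabetes.* The standardised RBG mean and mean square are 1.755 and 3.249 in the top band, and 0.490 and 0.390 in the middle band. Among the 122 tested:

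- mean = (72 × 1.755 + 50 × 0.490)/122 = 1.236
- variance v = (72 × 3.249 + 50 × 0.390)/122 − 1.236² = 0.549
- tested r = ρ√v / √(ρ²v + 1 − ρ²)

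For ρ = 0.50: 0.370/√(0.137 + 0.750) = 0.39.

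*With known diabetes on both sides.* The screened-population correlation is (ρ + 0.1 × 0.9 × 2²)/(1 + 0.1 × 0.9 × 2²) = (ρ + 0.36)/1.36. For ρ = 0.50 this is 0.63. In those tested, the 122 and the 80 are mixed. For ρ = 0.50 the covariance is 0.616 and the variances are 0.867 (RBG) and 1.389 (HbA1c), so r = 0.616/√(0.867 × 1.389) = 0.56.

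| ρ without known diabetes | Tested, without known diabetes | Screened population, all | Tested, all |
|---|---|---|---|
| 0.30 | 0.23 | 0.49 | 0.44 |
| 0.50 | 0.39 | 0.63 | 0.56 |
| 0.70 | 0.59 | 0.78 | 0.71 |

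**5. How far this depends on the assumptions.** With ρ = 0.50 and the same bands, changing the shift for known diabetes gives these screened and tested values:

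- 1 SD: 0.54 and 0.40
- 2 SD: 0.63 and 0.56
- 3 SD: 0.72 and 0.75

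The direction reverses at 3 SD.

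**6. Would relabelling accuracy as primary be enough?** No. Assume people without known diabetes have median RBG 110–118 mg/dL (log-SD 0.25–0.28), median HbA1c 5.6% and log-scale correlation 0.4–0.8. Sensitivity of RBG ≥140 mg/dL is then 0.37–0.85 in all of them but 0.78–0.97 in those tested, unweighted. Specificity is 0.77–0.91 against 0.28–0.62. Weighting each tested person at 110–159 by that band's size divided by the number tested (324/50 = 6.48 in step 4) corrects that band if the 50 are a random sample. Below 110 the testing probability is zero, so no weight exists.

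**The case against.** The best defence is that accuracy is not neglected. The protocol commits to sensitivity, specificity and ROC areas with 95% confidence intervals allowing for clustering and stratification. The correlation has a stated use as a step towards a cut-off, and the analysis plan is to be final before database lock. All of that stands. It would be wrong to infer that accuracy goes unanalysed. It would also be wrong to infer that a high correlation would be declared a success, since no threshold for success is set. The lock provision limits the scope for choosing between the two primaries after seeing results, though the article itself still names both.

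A second objection is that the numerical distortion rests on invented distributions. That is correct, and step 5 shows how much it matters. The mechanism does not rest on them: HbA1c testing depends on RBG by design, and no adjustment is described.

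A reader might also set 0.50 (people without known diabetes) beside 0.56 (everyone tested) and conclude that the plan inflates the correlation. Those are different populations. Compared like for like, the tested value is the lower one under the main assumptions.

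**Conclusion.** The concern holds in this form. The article names two different primaries, Table 1 conflicts with the abstract on the reference test for diabetes, and the correlation cannot answer the stated aim. These points rest on the text alone.

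That the observed correlation will not be that of the screened population follows from the testing rule. Its size is only illustrative: about 0.1 lower in people without known diabetes (0.50 to 0.39) and about 0.07 lower with known diabetes in both groups (0.63 to 0.56), with a possible reversal if known diabetes lies further from the rest.

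It is tempting to go further and say that weighting would yield accuracy for everyone without known diabetes from the data as planned. The documents do not support this. Nobody in that group with RBG below 110 mg/dL receives HbA1c (45% of the group in the illustration, by assumption), and the article does not say how the 50 per cluster are chosen.

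**What to change.** Before the analysis plan is final, reconcile the abstract, Objectives, Table 1 and Outcomes to one primary outcome: AUC, with sensitivity and specificity, of the simple-test model and of RBG alone, against POC HbA1c-defined diabetes in participants without known diabetes. In Table 1, make POC HbA1c the reference for that comparison. Then:

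- choose the 50 per cluster at 110–159 mg/dL at random, and record how many were eligible;
- weight by the inverse of the HbA1c testing probability;
- restrict the primary accuracy claim explicitly to RBG of 110 mg/dL or above, and add sensitivity analyses over a range of assumed diabetes prevalence below 110;
- report the correlation as a descriptive secondary outcome, weighted, and separately for known diabetes.

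The cost is a narrower accuracy claim, a random draw in each cluster and modest extra analysis. If the 50 were not drawn at random, the weights rest on an assumption that should be stated. A claim covering RBG below 110 would need HbA1c measured in a random sample of that group, which is a change of design and not of wording.
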